### 8.1.3. Endpoints

**Primary objective:**

To compare the virological efficacy of etravirine-based regimen with standard PI-containing regimens.

- The percentage of patients who experienced virologic failure throughout the 48 weeks of the study. Virologic failure will be defined as an increase in HIV RNA >50 copies in 2 determinations within 1 month.
- Time to virologic failure, defined as an increase in HIV RNA >50 copies in 2 determinations within 1 month. The first date with VL > 50 will be used to calculate time to virologic failure.
- Determination of antiretroviral resistance at the time of virological failure and comparison with baseline.

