## 6.2. INCLUSION CRITERIA

1. Adult patient having a diagnosis of HIV-1 infection.
2. Antiretroviral therapy started at least 12 months before, always with a HAART combination including 2 NRTIs plus a PI
3. Current HAART combination including 2 NRTIs plus a PI.
4. Maintained undetectable plasma HIV-1 RNA (VL < 50 copies/mL) since the beginning of antiretroviral therapy, for at least 6 months.
5. Absence of suspected or documented resistance mutations in the RT associated to NNRTIs or to any NRTI.
6. Patient having at least one of the following conditions:

- Dyslipemia (LDL cholesterol >130 mg/dL or triglycerides > 350 mg/dL) derived from their current PI regimen or current use of lipid lowering agents due to dyslipemia,
- Antiretroviral-related gastrointestinal disturbances, or
- Low patient’s satisfaction associated with the current regimen posology (BID regimen, ritonavir use, ritonavir intolerance…).

1. Good treatment adherence.
2. Voluntary written informed consent.

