## 6.5. SECURITY CRITERIA

The following safety procedures will be implemented:

- HIV-1 RNA levels will be performed in both treatment arms at week 4 of the study and every 12 weeks thereafter up to week 48.
- An interim evaluation will be performed when 75% of subjects reach week 24 of follow-up. The study will be prematurely interrupted at week 24 if the difference in rates of virological failure between study arms is 10% or higher.

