## 6.6. WITHDRAWAL AND DROPOUT CRITERIA

The patients will complete the clinical study before the stipulated time in the following circumstances:

- Virologic failure: it is defined as an increase in VL > 50 copies/mL on two consecutive visits.
- Interruption of treatment due to adverse events, intolerance or poor adherence during the study.
- Concurrent process or illness which in the opinion of the investigator requires the withdrawal of the patient.
- The patient does not wish to continue in the study.

If the study must be interrupted prematurely, all of the materials should be returned to the sponsor, at the *Lluita Contra la SIDA Foundation.*

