# 8.- TRIAL CONDUCTION AND RESPONSE EVALUATION

## 8.1. CRITERIA FOR RESPONSE EVALUATION

### 8.1.1. Principal Study Variable

Viral load at week 48.

Virologic failure is defined as an increase in HIV RNA >50 copies/mL in 2 determinations within 1 month. The first date with VL > 50 copies/mL will be used to calculate time to virologic failure.

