## 8.3. TRIAL DEVELOPMENT

After accepting the participation, patients would be assessed the first visit. Study visits would be at entry (BL) and weeks 4, 12, 24, 36 and 48.

Plasma samples will be stored at –80ºC.

Viral load, complete blood count, CD4 cells count, and a complete biochemistry and haematology will be performed at every visit (except for week 4 where only CD4 count and viral load will be performed).

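### Virologic failure needs a second value above 50 copies/mL, but no confirmatory sample is scheduled at any visit and planned testing ends at week 48, so a first rise at week 48 has no planned confirmation

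*Protocol*

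**What the plan says.** Section 8.1.3 lists, under the primary objective, "The percentage of patients who experienced virologic failure throughout the 48 weeks of the study" and a time-to-failure endpoint. Its definition is "Virologic failure will be defined as an increase in HIV RNA >50 copies in 2 determinations within 1 month", and 8.1.1 gives the same rule. Failure is dated back to the first raised value: "The first date with VL > 50 will be used to calculate time to virologic failure".

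Section 6.6, on withdrawal, defines failure differently: "Virologic failure: it is defined as an increase in VL > 50 copies/mL on two consecutive visits".

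On sampling, 8.3 states "Study visits would be at entry (BL) and weeks 4, 12, 24, 36 and 48", with viral load measured at every visit. Section 5.6 gives the same weeks, and week 48 is the last column of the flow chart. Section 6.5 adds "HIV-1 RNA levels will be performed in both treatment arms at week 4 of the study and every 12 weeks thereafter up to week 48". Sections 3.9 and 5.4 allow 72 weeks in all, made up of 24 for inclusion and 48 for follow-up.

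Section 8.1.1 also names a single measurement, "Viral load at week 48", as the principal study variable. Section 6.6.1 and the flow chart footnote make genotyping depend on virologic failure. No section describes a repeat viral load after a raised value, at week 48 or at any other visit.

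**The concern.** An event that needs two values can be ascertained only where a second value is taken. At week 48 none is planned, yet the endpoint is meant to cover the whole 48 weeks. Three outputs depend on this:

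- the failure percentage;
- the time-to-failure analysis, since from planned visits a failure first seen at week 48 cannot be confirmed;
- the resistance endpoint, since a rebound that never qualifies as failure triggers no genotype.

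The first hypothesis in 4.1 is that suppression rates will be comparable. If real failures in both arms go uncounted, the absolute difference between the arms shrinks, which favours that conclusion. With 20 patients per arm, one patient is 1/20 = 5 percentage points.

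**Working it through.** There is no figure in the plan to reproduce. Section 12.4 sets 40 patients as a pilot size, with no failure rate, margin or power. The check compares the visit gaps with each confirmation rule and then gives an illustration of size.

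**Step 1. Visit gaps.** The visits in 8.3 fall at weeks 0, 4, 12, 24, 36 and 48, so the gaps are 4, 8, 12, 12 and 12 weeks. Section 6.5 read literally gives weeks 4, 16, 28 and 40, with the next at 52. That does not match 8.3 and should be tidied. I use the 8.3 schedule; on either reading nothing is planned after week 48.

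**Step 2. Consecutive-visits rule (6.6).** A first rise at week 4, 12, 24 or 36 can be confirmed at the next visit. The week-48 sample can confirm a week-36 rise, which is then dated week 36. A first rise at week 48 has no next visit. Rebounds arising after the week-36 sample, in the last 12 of 48 weeks (12/48 = 25% of follow-up), cannot become failures from planned visits.

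**Step 3. One-month rule (8.1.1, 8.1.3).** One month is about 4.35 weeks. The only planned pair that close together is baseline and week 4. Baseline is expected to be below 50, because inclusion requires "Maintained undetectable plasma HIV-1 RNA (VL < 50 copies/mL) since the beginning of antiretroviral therapy, for at least 6 months". Planned visits therefore confirm no rise at week 4, 12, 24, 36 or 48. Every failure under this rule needs an unscheduled repeat, and the protocol provides for none. If repeats are made but only within the 48 weeks, rises first seen at planned visits up to week 36 can be confirmed and those first seen at week 48 cannot.

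**Step 4. Illustrative size for Step 2, or for repeats confined to the 48 weeks.** Assumptions, none of them from the protocol: constant hazard, and a true 48-week failure risk p of 5%, 10% or 20% in an arm of 20.

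- Risk by week 36: F(36) = 1 − (1 − p)^(36/48)
- Share first visible at week 48: (p − F(36)) / p
- Patients per arm: 20 × (p − F(36))

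| p | F(36) | p − F(36) | Share | Patients per arm | Expected failures, 20p |
|---|---|---|---|---|---|
| 5% | 3.8% | 1.2% | 24.5% | 0.25 | 1 |
| 10% | 7.6% | 2.4% | 24.0% | 0.48 | 2 |
| 20% | 15.4% | 4.6% | 22.9% | 0.92 | 4 |

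If one arm had a true risk of 5% and the other 20%, the difference of 15 points would appear as 15.4 − 3.8 = 11.6 points.

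**The case against.** The strongest reply is that the one-month rule, which belongs to the endpoint, presupposes unscheduled repeats. Nothing forbids one after week 48, and because failure is dated at the first value, a repeat a few weeks later would give a failure dated at week 48, inside the endpoint window. This stands. It rules out an inference a reader might draw, that the last quarter of follow-up can contribute no failures and that the 48-week percentage is really a 36-week percentage. That pattern follows only from the rule in 6.6, or from repeats confined to the 48 weeks. An unscheduled sample between weeks 36 and 48 could also catch a rebound.

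The reply does not supply the sample, however. Section 6.5 plans testing only to week 48, and the 72-week study duration leaves the last patient included no time for a later draw.

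A second tempting inference is that late rebounds are counted as suppressed. No section says so, and the single week-48 viral load in 8.1.1 would show the rebound directly. That mitigates the problem, but it also means a patient can be above 50 copies/mL on the principal variable without being a failure in 8.1.3.

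Third, how to classify an unconfirmed last value is commonly left to the analysis plan, which is not shown here. I accept that and do not treat silence on classification as the fault. The sampling is different, because an analysis plan cannot create a blood sample that was not drawn.

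Last, the expected loss is below one patient per arm in an exploratory pilot. That is true and limits the weight of the point.

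**Conclusion.** The point holds in a limited form. Both definitions require a second value, no confirmatory sample is scheduled at any visit, and planned testing ends at week 48. Under the rule in 6.6, or with repeats confined to the 48 weeks, no failure can be dated after week 36 from planned visits, and a patient with a first rise at week 48 gets no failure-triggered genotype. Under the rule in 8.1 the problem is not peculiar to week 48: the definition depends throughout on repeats that the protocol does not provide for.

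The documents do not show that confirmation after week 48 is impossible. What they show is that it is not planned.

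The size, about 23% to 25% of failures and 0.25 to 0.92 patients per arm, rests entirely on the assumed constant hazard and assumed risks. It is small in absolute terms, but the correction is cheap and changes who counts as a failure and who is genotyped, so it should be made.

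**What to change.** 1. Reconcile the failure definitions in 6.6 and 8.1. This point concerns how the endpoint is ascertained; the withdrawal rule itself is for the sponsor to settle.
2. State in 8.1.1, 8.1.3 and the flow chart that any viral load above 50 copies/mL, including one first observed at week 48, is repeated within 1 month and, if confirmed, counts as virologic failure dated at the first value.
3. Report separately any week-48 value above 50 copies/mL that has no repeat, with a sensitivity analysis that counts it once as failure and once as non-failure. Counting an unrepeated single value as failure in the main analysis would depart from the two-value definition, and I do not ask for it.
4. Bring the testing weeks in 6.5 into line with the visits in 8.3.

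The cost is protocol wording, one extra viral load in each of the few patients affected, and up to 4 more weeks of follow-up for those whose first raised value is at week 48. The 72-week limit in 3.9 and 5.4 needs a matching allowance.

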### 6.6.1. Medical Approach to Withdrawal

In all cases in which the treatment is concluded prematurely for any reason, detailed information will be given about the date and reasons of the discontinuation to the promoter.

The investigator will facilitate the necessary medical support to the patient who discontinues the study prematurely due to treatment failure or to the appearance of an adverse event or a related concurrent illness.

In case of virologic failure,

- Genotypic resistance testing will be performed to all participants experiencing virologic failure during the study.
- A salvage regimen will be optimized according to genotypic resistance testing and previous antiretroviral treatment history.

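### Virologic failure has two definitions (8.1.1/8.1.3 versus 6.6), and the 1-month endpoint version depends on a repeat viral load that no section requires

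*Protocol*

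**What the plan says.** The endpoint sections agree with each other. Section 8.1.1 states: "Virologic failure is defined as an increase in HIV RNA >50 copies/mL in 2 determinations within 1 month". Section 8.1.3 repeats this for the failure percentage ("Virologic failure will be defined as an increase in HIV RNA >50 copies in 2 determinations within 1 month") and for time to failure, and both sections date failure at the first value above 50.

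Section 6.6, which lists the reasons for leaving the study early, defines the same term in another way: "Virologic failure: it is defined as an increase in VL > 50 copies/mL on two consecutive visits". It sets no time limit between the two values.

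On sampling, section 8.3 says "Study visits would be at entry (BL) and weeks 4, 12, 24, 36 and 48" and "Viral load, complete blood count, CD4 cells count, and a complete biochemistry and haematology will be performed at every visit". Week 4 is a reduced visit, but viral load is still measured there. Section 5.6 gives the same follow-up weeks. Section 6.5 describes the monitoring as "HIV-1 RNA levels will be performed in both treatment arms at week 4 of the study and every 12 weeks thereafter up to week 48".

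Two further rules use the term without saying which definition applies. Section 6.6.1 says: "Genotypic resistance testing will be performed to all participants experiencing virologic failure during the study". Section 6.5 says: "The study will be prematurely interrupted at week 24 if the difference in rates of virological failure between study arms is 10% or higher".

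**The concern.** One term carries two definitions, and the protocol's own schedule can satisfy only one of them after baseline. The endpoint version needs two values inside a month, but viral load is tied to visits that are further apart than that. Whether a patient can become an endpoint failure on study therefore depends on an unscheduled draw that the wording implies but nothing orders.

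The failure percentage, time to failure and resistance at failure (8.1.3), withdrawal (6.6), genotyping and salvage treatment (6.6.1) and the interim stopping rule (6.5) all use this term. If the definitions are not aligned, a patient can be treated as a failure in the clinic and not be one in the primary endpoint.

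This cannot be left to a later analysis plan. Such a plan could choose a definition, but it could not supply samples that were never drawn, and it does not govern withdrawal and genotyping while the trial runs.

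**Working it through.** The protocol states no figure to reproduce here. The check compares the gaps between scheduled viral loads with the 1-month window, then applies both definitions to example patients.

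**Inputs.** Visits at baseline and weeks 4, 12, 24, 36 and 48 (5.6, 8.3), with viral load at each (8.3). Window of 1 month (8.1.1, 8.1.3), taken as 28, 30 or 31 days; the result is the same for all three.

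**Gap in days = (later week − earlier week) × 7.**

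| Successive pair | Gap | Within 1 month? | Consecutive visits (6.6)? |
| --- | --- | --- | --- |
| Baseline to week 4 | 4 × 7 = 28 | yes | yes |
| Week 4 to 12 | 8 × 7 = 56 | no | yes |
| Week 12 to 24 | 12 × 7 = 84 | no | yes |
| Week 24 to 36 | 12 × 7 = 84 | no | yes |
| Week 36 to 48 | 12 × 7 = 84 | no | yes |

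After baseline, 0 of 4 pairs can meet the 1-month rule and 4 of 4 can meet the 6.6 rule. The smallest post-baseline gap is 56 days.

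**The baseline/week-4 pair.** It fits the window, but section 6.2 requires a viral load below 50 at entry. A baseline value above 50 is still possible, because the flow-chart footnote in 8.3 accepts a screening test up to 3 months old. It would show viremia already present at entry, not failure of the assigned regimen.

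**Both definitions applied to the same patient.**

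| Pattern | 8.1.1/8.1.3 | 6.6 |
| --- | --- | --- |
| Above 50 at weeks 12 and 24, no draw in between | not a failure | failure: withdrawn, then genotyped under 6.6.1 |
| Above 50 at week 24 and on a repeat within a month, below 50 at week 36 | failure | failure only if the repeat counts as a visit |
| First value above 50 at week 48, no further draw | not a failure | not a failure |

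The first two rows show that the definitions can part in either direction. In the third they agree only because no confirming sample is required, so a true late failure and a transient rise look the same.

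**Is a repeat required elsewhere?** Sections 5.6, 6.5, 6.6.1 and 8.3 contain no such instruction. The cell marks of the flow chart are not legible in the text at hand, but its columns (screening, baseline, weeks 4, 12, 24, 36, 48) and its footnotes show no confirmation visit, and the written sections fix the schedule on their own.

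**The case against.** The strongest reply is that the endpoint itself is consistent and the texts can largely be reconciled. Sections 8.1.1 and 8.1.3 give one rule, and they speak of determinations, not visits, so they evidently expect a confirmatory draw. A patient recalled for that draw has arguably made a further visit and then meets 6.6 as well. Section 12.4 describes the trial as closely monitored, so a first value above 50 may seldom go 12 weeks without a repeat. On this view only a written instruction is missing. Section 6.5 gives no definition of its own, so its natural reading is the efficacy definition in 8.1.

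Much of this stands. It narrows the problem to patients without a repeat inside a month. It does not remove it, because the repeat is implied and not required, and 6.6 does not present its wording as a separate withdrawal trigger: it defines the same term.

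Some stronger readings are tempting but not supported:

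- A reader might infer that the primary endpoint can never be met. An unscheduled draw would meet it, and nothing forbids one.
- A reader might infer that section 6.5 sets a second, conflicting schedule. Weeks 12, 24, 36 and 48 are themselves 12 weeks apart, so its wording is best read as a loose description of the 8.3 schedule.
- A reader might infer bias between arms, since the trial is open-label and retesting is discretionary. Retesting could differ by arm, but nothing in the protocol shows that it would.
- A reader might measure the defect by what one patient contributes to the arm difference in 6.5. That share reflects the small sample, not how many patients would be reclassified.

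**Conclusion.** The point holds as an internal inconsistency that is wrong as written and should be fixed. Followed literally, the protocol withdraws and genotypes a patient as a virologic failure whom its primary endpoint does not count, leaves a first value above 50 at week 48 without required confirmation, and does not tie the stopping rule to either definition.

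The firm figure is structural: 0 of 4 scheduled post-baseline pairs fit the endpoint window. The protocol gives no rate of values above 50 and no retesting practice, so the number of patients affected is unknown and could be zero. The conclusion rests on the conflict in the text and the visit schedule, not on a demonstrated effect on results. It also assumes that the case report form, which is attached to the protocol but not shown, does not itself order a repeat.

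A reader might go on to infer that a planned significance test of the primary endpoint is invalid. The protocol does not support that: section 12.2 names no test of the failure percentage. What is exposed is the failure count, the time to failure and the interim decision.

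**What to change.** Use one definition in 6.5, 6.6, 8.1.1 and 8.1.3: two consecutive viral load determinations above 50 copies/mL, dated at the first, with no hard time window on counting failure.

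Add to 5.6 and 8.3 that any value above 50 in either arm, including at week 48, triggers a repeat viral load within 4 weeks. If that repeat is missed or late, the next available value confirms or refutes failure. Withdrawal (6.6) and genotyping (6.6.1) then follow the confirmed value. For a first rise at week 48, the repeat would fall no later than week 48 + 4 = 52, so the text should allow a draw after the last scheduled visit.

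Simply copying the 1-month rule into 6.6 would be worse. A patient above 50 at weeks 12 and 24 whose repeat was missed would then meet neither the endpoint nor the virologic-failure withdrawal criterion, and genotyping would not be triggered. The current 6.6 wording at least catches that patient.

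The cost is protocol wording and a few extra viral load tests, limited to patients with a value above 50.

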**Secondary objectives:**

To compare the immunological efficacy of etravirine-based regimen with standard PI-containing regimens.

- Changes in CD4+/CD8+ T lymphocytes at week 48 from baseline.

To compare the tolerability and toxicity of etravirine-based regimen with standard PI-containing regimens.

- Changes in lipid parameters (total, HDL-, LDL-cholesterol and triglyceride levels) at week 48 relative to baseline values.
- Changes in the administration of lipid-lowering drugs throughout the study (new administrations or the withdrawal of previous lipid-lowering drugs).
- Percentage of patients who withdraw from the study.
- Percentage of patients who withdraw from the study due to toxicity.
- Percentage of patients with toxicity ≥ grade 3.

To compare the cardiovascular risk of etravirine-based regimen with standard PI-containing regimens.

- Changes in cardiovascular risk estimated by changes in the SCORE equation at week 48 relative to baseline values.

To compare patient’s satisfaction of etravirine-based regimen with standard PI-containing regimens.

- Changes in patient’s satisfaction at week 48 from baseline, using a 100 mm analogue visual scale.

## 8.2. PROCEDURES FOR THE STUDY PARAMETERS

### 8.2.1. Clinical History and Physical Examination

Demographic and HIV infection-related data will be collected in order to characterize the study population (sex, age, time since HIV diagnosis, risk factor, clinical stage, history of opportunistic infections or tumours and previous antiretroviral treatment).

A complete physical examination will be performed at the baseline visit, including weight and height. In the follow-up, a physical exam will be performed.

In baseline and W48, in order to calculate the cardiovascular risk using the SCORE equation, smoking habits will be recovered and blood pressure will be measured.

### 8.2.2. Laboratory Test

Patients will fast for at least 8 hours prior to assessment, in the points specified in the flow chart of the study (section 8.3). The following parameters will be quantified, as needed:

- **Haematology:**

Leucocyte Hemoglobin

Lymphocyte count Hematocrit

Red blood cell count Platelet count

- **Biochemistry:**

Glucose Alanine aminotransferase (ALT)

Urea Gamma‑GT (GGT)

Creatinine Alkaline phosphatase

SodiumTotal Cholesterol

Potassium HDL Cholesterol

Total Bilirubin LDL Cholesterol

Total Protein Triglycerides

Aspartate aminotransferase (AST)

- **Immunology**

CD4/CD8 Index

CD4 / CD8 percentage

CD4 / CD8 count

- **Microbiology**

Viral load

- **Pregnancy test in urine in women**

**Note: Before the beginning of the study, all labs will facilitate to the sponsor and to the investigator a list of the reference normal values of the parameters to evaluate during the study.**

